| **Type of visit/contact** | | | | | | **Triage** | | | **Vaccine 1** | | | **Contact 1** | | **Safety 1** | | **Vaccine 2** | | | **Contact 2** | | **Safety 2** | | **Immunity** | | | **Contact 3** |  |
| --- | --- | --- | --- | --- | --- | --- | --- | --- | --- | --- | --- | --- | --- | --- | --- | --- | --- | --- | --- | --- | --- | --- | --- | --- | --- | --- | --- |
| **Visit** | | | | | | **T** | | | **V1** | | | **C1** | | **S1** | | **V2** | | | **C2** | | **S2** | | **I** | | | **C3** |  |
| Programmed visit | | | | | | V1  (-30)d | | | V1 | | | V1+3 (+2)d | | V1+7  (+3)d | | V1+28  (+7)d | | | V2+3  (+2)d | | V2+7  (+3)d | | V2+28  (+7)d | | | V2+194  (+7)d |  |
| **Procedures** | | |  | | | | | | |  |  |  |  |  |  |  |  |  |  |  |  |  |  |  |  |  |  |
| Information and written informed consent | | | | | | X | | |  | | |  | |  | |  | | |  | |  | |  | | |  |  |
| Check/confirm inclusion/exclusion criteria | | | | | | X | | | X | | |  | |  | | X | | |  | |  | |  | | |  |  |
| Collect baseline demographic data | | | | | | X | | |  | | |  | |  | |  | | |  | |  | |  | | |  |  |
| Collect/review medical history | | | | | | X | | | X | | |  | | X | | X | | |  | | X | | X | | |  |  |
| Perform targeted physical examination | | | | | | X | | | X | | |  | | X | | X | | |  | | X | | X | | |  |  |
| Evalute potential for pregnancy^†^ | | | | | | X | | | X | | |  | |  | | X | | |  | |  | | X | | |  |  |
| Randomization | | | | | |  | | | X | | |  | |  | |  | | |  | |  | |  | | |  |  |
| Observe for immediate reactions for 30 minutes | | | | | |  | | | X | | |  | |  | | X | | |  | |  | |  | | |  |  |
| Evaluate solicited adverse events | | | | | |  | | | X | | | X | | X | | X | | | X | | X | | X | | |  |  |
| Survaillance of unsolicited adverse events | | | | | |  | | | X* | | | X | | X | | X | | | X | | X | | X | | | X |  |
| Update contact information | | | | | |  | | | X | | | X | | X | | X | | | X | | X | | X | | |  |  |
| **Intervention** | | | | | |  | | |  | | |  | |  | |  | | |  | |  | |  | | |  |  |
| Vacination | | | | | |  | | | X | | |  | |  | | X | | |  | |  | |  | | |  |  |
| **Participant diary** | | | | | |  | | |  | | |  | |  | |  | | |  | |  | |  | | |  |  |
| Deliver diary and thermometer | | | | | |  | | | X | | |  | |  | | X | | |  | |  | |  | | |  |  |
| Instruct participant on use of diary and thermometer | | | | | |  | | | X | | |  | |  | | X | | |  | |  | |  | | |  |  |

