During the first week following each study injection, participants will be asked to record local and systemic signs and symptoms using preprinted Participant Diary, a thermometer, and a a local reaction measurement device. In addition to solicited signs, participants will be asked to report any other adverse events. Concomitant medications will also be recorded. Members of the investigator’s clinical team will have contact with participants via phone (C1) on Day 3 (+2) after study injection to check that participants are correctly completing the Participant Diary and to check on the participants’ well-being (occurrence of solicited and unsolicited adverse events).

Participants will return to the study site seven days after study injection, visit S1 on V1+7 (+3) days. At that time, the Principal Investigator or designee will review the Participant’s Diary, confirm the information included and transcribe all solicited and other adverse events onto source document and the case report forms. Blood will be collected for selected biochemical and hematological blood tests. Results of the laboratory tests must be reviewed by the study physician. The study physician will determine the severity grade of laboratory results using the Toxicity Table for Grading Severity of AEs (see section 9). If the result is Grade 2 or higher and clinically significant, the study physician will request repeat laboratory tests. Laboratory results that are Grade 2 or higher and considered to be clinically significant will be followed by the study physician until resolution or stabilization. “Clinically significant” means that the result warrants further medical investigation or treatment because it may have impact on a person’s health status.

Participants will then return to the study clinic 4 weeks after administration of the first study injection (Day 28 + 7). Interim medical histories and concomitant medications will again be reviewed with the participant and blood specimens will be collected for immunogenicity analyses. At visit V2, Day 28 (+7), participants will receive a second study injection (women will have a urine pregnancy test beforehand). If a women is found to be pregnant she will not receive the second study injection and counseling will be provided to them. Blood specimens will be collected for immunological testing prior to administration of study injection. Participants will be carefully monitored for adverse reactions for 30 minutes after study injection.

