During the next 7 days following study injection, participants will be asked to record local and systemic signs and symptoms using a Participant Diary, a thermometer, and a local reaction measurement device. Concomitant medications will also be recorded. In addition to solicited signs, participants will be asked to report any other adverse events. Members of the investigator’s clinical team will have contact with participants via phone (C2) 3 days (+2) after study injection to check that participants are correctly completing the Participant Diary and to check on the participants’ well-being.

On the S2 visit, participants will return to the study site seven days after the second study injection, V2+7 (+3) days. At that time, the Principal Investigator or designee will review the Participant’s Diary, confirm the information included and transcribe all solicited and other adverse events onto the case report forms. Blood will be collected for selected biochemical and hematological blood tests as well as immunogenicity testing. Results of the safety laboratory tests will be reviewed by the study physician. The study physician will determine the severity grade of laboratory results using the Toxicity Table for Grading Severity of AEs (see section 9). If the result is Grade 2 or higher and clinically significant, the study physician will request repeat laboratory tests. Laboratory results that are Grade 2 or higher and considered to be clinically significant will be followed by the study physician until resolution or stabilization. “Clinically significant” means that the result warrants further medical investigation or treatment because it may have impact on a person’s health status.

On the I visit, participants will then return to the study clinic 3 weeks after administration of the second study injection, V2+28 (+7) days. Interim medical histories and concomitant medications will again be reviewed with the participant and blood specimens will be collected for immunogenicity analyses.

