### 7.2.3 Seventh Day after Study Injection (visit S1)

1. Study staff will confirm participant identity.
2. Study staff will review the Participant Diary and interim history with the participant and inquire about any new medical events since medical histories were last updated. Any AEs that have occurred will be recorded in the appropriate CRFs.
3. A study clinician will perform a targeted physical examination and record the information on the CRF. Results will be reviewed by study staff and with the participant and any AEs that have occurred will be recorded in the appropriate CRF.

Blood specimens will be collected for testing selected biochemical parameters (total bilirubin, ALT, AST, creatinine) and selected hematologic studies (WBC, Hgb, and platelets). Specimen collection information must be documented on the CRF and in specimen collection logs. About 9 mLs of blood will be collected.

1. Laboratory results will be reviewed within 36 hours of receipt by the study physician. Any out-of-normal-range result Grade 2 and above will be evaluated by the study physician to assess whether it is of clinical significance and whether it is related to vaccination. Laboratory results that are Grade 2 or above and considered to be clinically significant will be followed by the study clinician until resolution or stabilization.
2. The participant will be instructed to inform the study staff as soon as possible if he/she experiences an AE requiring medical care and to seek medical care as appropriate. If the participant visits a health care provider, the participant should be sure to inform the health care provider of participation in this study and give the health care provider the contact information for the investigator. Study staff may request to review any document related to participant´s visits or hospitalizations handed to study staff by participants (e.g.: hospital discharge summaries, etc), and considered relevant to the assessment of potential adverse events, and if permitted by the participant, extra information may be requested by study staff to other health care services/providers.

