## 9.3 Methods and Timing for Assessing and Recording Safety Parameters

### 9.3.1 Adverse Events

The occurrence of an AE might come to the attention of study personnel during study visits and interviews of a study participant presenting for medical care. Information to be collected on AEs includes event description, time of onset, clinician’s assessment of severity, relationship to study product, and time of resolution/stabilization of the event. AE assessment should be made only by those with the training and authority to make a diagnosis.

Any medical condition that was present at the time that the participant was enrolled should not be reported as an AE, but should be reported as a pre-existing condition on the Medical History Form. However, if this condition occurs with greater frequency or severity during the study, it should be recorded as an AE.

AEs, including laboratory abnormalities that are Grade 2 and above, should always be assessed for severity and relationship to study products.

This study will collect and record solicited and unsolicited local and systemic AEs (described in further detail in section below). For clarity, solicited AEs refer specifically to those asked about during the 7-day post study injection period. Unsolicited events are those not specifically solicited, but may be reported by the participant at any time or observed by study staff while the participant is at a clinic for a study visit. Unsolicited events are recorded up through 28 + 7 days post each study injection, except for SAEs, which are recorded throughout the entire study period as required (V2+194 days). If a new solicited event is reported by the participant outside of the 7-day post-vaccination window, this event will be recorded as an “unsolicited AE” because it will be outside of the 7-day window for collection of solicited reactogenicity.

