**Table 6 Classification of the severity of the unsolicited clinical adverse events.**

| **Adverse event** | **Grade 1** | **Grade 2** | **Grade 3** | **Grade 4** |
| --- | --- | --- | --- | --- |
| Clinical adverse event (as defined by this protocol) | Does not interfere  with daily activities | Mild interference with daily activities | Prevent daily activities | Emergency department visit*  OR  Hospitalization |

* It requires 12 hours or more of admission to a ward or emergency department for the management of the adverse event.

All cases of death will have their severity classified as Grade 4.

The worst severity reported to an adverse event, until its resolution or conclusion, will be the severity used to perform the study analysis.

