### 9.3.6 Unsolicited Adverse Events

Unsolicited adverse events are any AEs that occur any time after the vaccine/placebo is given (temporally related to study product), whether or not deemed “related” to the product, and are not solicited (not specifically asked of the participant). Unsolicited AEs can be observed by study staff while the participant is at a clinic for a study visit or reported by the participant at any time. Any solicited sign or symptom starting after 7 days post- each vaccination will be recorded as an “unsolicited AE”.

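### Section 9.3.1 sorts solicited symptoms by the date they are reported, while 9.3.6 and 11.5 go by onset or occurrence, so an in-window reaction first elicited after day 7 has two possible classes

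*Protocol*

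**What the plan says.** Two sentences of the Protocol decide when a symptom on the solicited list is recorded as unsolicited.

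- Section 9.3.1: "If a new solicited event is reported by the participant outside of the 7-day post-vaccination window, this event will be recorded as an" unsolicited AE, and the reason given is "because it will be outside of the 7-day window for collection of solicited reactogenicity".
- Section 9.3.6: "Any solicited sign or symptom starting after 7 days post- each vaccination will be recorded as an" unsolicited AE.

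Section 11.5 defines the reactogenicity category by reactions occurring through 7 days after any dose. Section 9.2 reports solicited local, solicited systemic and unsolicited events as separate percentages.

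On timing, Section 4 states "Participants will return to the study site seven days after study injection, visit S1 on V1+7 (+3) days" and, for S2, "participants will return to the study site seven days after the second study injection, V2+7 (+3) days". At S1, under Section 7.2.3, "Study staff will review the Participant Diary and interim history with the participant and inquire about any new medical events"; Section 7.2.7 has the same step at S2. In Table 1 the row "Evaluate solicited adverse events" is marked at V1, C1, S1, V2, C2, S2 and I.

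On severity, Table 4 covers solicited clinical events with symptom-specific criteria. Table 6 is titled "Classification of the severity of the unsolicited clinical adverse events" and uses one functional scale. Section 9.3.5 adds that redness, swelling and induration are always graded by size.

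**The concern.** One rule looks at when the participant speaks, the other at when the symptom began. They agree for most events. They part when a symptom begins within seven days of an injection but first comes to light after that. Site staff completing the CRF then have two incompatible instructions, and the one in 9.3.1 also departs from the definition used in the analysis section.

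Two things are at stake. The solicited local and systemic percentages in 9.2 would depend partly on the day a visit happens to fall and on when a participant mentions a symptom. And because class is tied to the severity table, the same reaction could be graded on different criteria. Candidate selection rests on safety as well as immunogenicity (Section 2.2.1), so these rates should have one definition.

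**Working it through.** The Protocol states no figure to reproduce here. The check sets the rules against the visit schedule and then compares the two severity tables.

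**1. Does 9.3.1 really use report date?** Its verb is reported. Its reason is the window for collection. The same paragraph defines solicited events as those asked about during the 7-day period. All three point to the time of asking or reporting. Sections 9.3.6 (starting) and 11.5 (occurring) point to the time of the event.

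**2. Where can the rules disagree?** Only for an onset inside the window with a first report outside it.
- S1 and S2 are permitted on days 7, 8, 9 and 10 after the injection. Three of those four days (8, 9, 10) lie outside the window.
- The history review at V2, before the second injection, falls 28 to 35 days after dose 1. Visit I falls 28 to 35 days after dose 2. Both lie wholly outside the window of the preceding dose.
- A diary entry made in the window and transcribed at a late S1 or S2 is not affected. Nor is a symptom told at C1 or C2, which fall on days 3 to 5.

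**3. A record that falls between the rules.** Headache on day 1, not in the diary, not mentioned at C1, first mentioned at S1 on day 9: solicited under 9.3.6 and 11.5, unsolicited under 9.3.1.

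**4. What does the change of class do to severity?** Comparing the twelve symptoms of Table 4 with Table 6:
- Same criteria (4): pruritus, fatigue/malaise, myalgia, arthralgia.
- Different criteria (8): pain, erythema, swelling/induration, ecchymosis, nausea/vomiting, fever, chills, headache.
- Section 9.3.5 keeps erythema and swelling/induration on size, so 8 − 2 = 6 remain: pain, ecchymosis, nausea/vomiting, fever, chills, headache.
- Example: a fever of 39.2 °C that does not interfere with daily activities is Grade 3 in Table 4 (39.0 to 40.0 °C) and Grade 1 in Table 6.

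**5. Size per event.** With 54 participants per arm (Section 11.1), one reclassified participant changes the arm's solicited rate by 1/54 = 1.85 percentage points.

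Illustration only, since the Protocol gives neither a reaction rate nor a late-report share. Assume 20 of 54 participants have an in-window reaction, so an onset rule gives 20/54 = 37.0% (exact 95% CI 24.3 to 51.3). Under the report-date rule:
- 1 first reported late: 19/54 = 35.2%
- 3 first reported late: 17/54 = 31.5%
- 5 first reported late: 15/54 = 27.8%

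**The case against.** The best defence is that this is one loose sentence. The word new in 9.3.1 may have been meant as new onset, the paragraph refers the reader to more detail below, and both 9.3.6 and 11.5 use onset or occurrence. The daily diary, the thermometer and measuring device, and the day-3 call should leave few in-window reactions to surface late. All of this bears on size, and it stands. It does not remove the conflict, because the reason that 9.3.1 gives is about collection and not onset.

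A reader might infer four stronger points, which the documents do not support:

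- *Large measured reactions would be downgraded.* Not erythema or swelling/induration: 9.3.5 always grades these by size. Section 9.3.5 also calls for predefined scales where available, so even for fever the move to Table 6 is possible rather than certain.
- *No event newly reported at V2 could be solicited.* V2 is also the second injection day, and the Table 1 mark there covers immediate reactions to that dose, which are inside a new window. Only the mark at I lies wholly outside a window.
- *The primary safety count is biased downward.* The endpoint in 3.1 pools solicited and unsolicited reactions over 7 days, so a reclassified in-window reaction stays in the any-reaction count.
- *The arms would be affected differently.* The same rule applies in every arm and assessors are blinded; nothing in the Protocol shows a differential loss.

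**Conclusion.** The contradiction is in the current text, and 9.3.1 is wrong as worded because it conflicts with both 9.3.6 and the analysis definition in 11.5. Its reach is narrow: listed symptoms with onset in the window that both the diary and the C1 or C2 call missed. For those events, following 9.3.1 lowers the separate solicited percentages in 9.2 by 1.85 points per participant in a 54-person arm. It may also change the grading criteria for about six of the twelve symptoms. How many events this involves cannot be computed from the documents, and the illustrative rates rest on assumed counts. The issue is minor but worth correcting, since it is a recording instruction that sites apply as data are entered.

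**What to change.** In Section 9.3.1, make the test whether the symptom has its onset outside the 7-day window, in place of whether the participant reports it outside the window. That matches 9.3.6 and 11.5. Add one sentence: a listed sign or symptom with onset inside the window is recorded as solicited and graded by Table 4 whenever it is reported, and is flagged if it was first recalled after the window. Carry the same rule into the eCRF completion instructions.

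The cost is this change to 9.3.1 and the matching eCRF instruction. No new data are needed, because 9.3.1 already requires time of onset for every AE. The small downside is that a few solicited events will rest on recall at a visit instead of a same-day diary entry; the flag lets these be examined separately.

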### 9.3.2 Severity of Event

The severity of the solicited clinical adverse events (local and systemic), laboratory events and unsolicited AEs will be classified by a numeric scale ranging from 1 to 4, according to Table 4, 5, 6, created based on the FDA guidance.^[[22]](#endnote-23)^

**Table 4 Classification of the severity of the solicited clinical adverse events.**

| **Solicited Local Adverse Events** | | | | |
| --- | --- | --- | --- | --- |
| **Adverse Event** | **Grade 1** | **Grade 2** | **Grade 3** | **Grade 4** |
| Pain/tenderness at the injection site of the investigational product | Does not interfere  with daily activities | Repeated use of non-narcotic analgesic >24 hours  OR  Mild interference with daily activities | Any use of a narcotic analgesic  OR  Prevent daily activities | Emergency department visit*  OR  Hospitalization |
| Erythema at the injection site of the investigational product ^†^ | 25 – 50 mm | 51 – 100 mm | >100 mm | Necrosis  OR  Exfoliative dermatitis |
| Swelling/Induration at the injection site of the investigational product ^†^ | 25 – 50 mm | 51 – 100 mm  OR  Mild interference with daily activities | >100 mm | Necrosis |
| Ecchymosis at the injection site of the investigational product ^†^ | 25 – 50 mm | 51 – 100 mm | >100 mm | Necrosis |
| Pruritus at the injection site of the investigational product | Does not interfere  with daily activities | Mild interference with daily activities | Prevent daily activities | Emergency department visit*  OR  Hospitalization |
| **Solicited Systemic Adverse Events** | | | | |
| Nausea/vomiting | Does not interfere  with daily activities  OR  1 to 2 episodes in 24 hours | Mild interference with daily activities  OR  More than 2 episodes in 24 hours | Prevent daily activities, it requires IV hydration | Emergency department visit*  OR  Hospitalization  OR  Hypovolemic shock |
| Fever | 37.8 – 38.4°C | 38.5 – 38.9°C | 39.0 – 40.0°C | >40°C |
| Chills | Slight cold sensation; chills, teeth chatter | Moderate chills in the entire body, it requires the use of narcotics | Serious or prolonged, no response to narcotics | ----- |
| Headache | Does not interfere  with daily activities | Repeated use of non-narcotic analgesic >24 hours  OR  Mild interference with daily activities | Any use of a narcotic analgesic  OR  Prevent daily activities | Emergency department visit*  OR  Hospitalization |
| Fatigue/malaise | Does not interfere  with daily activities | Mild interference with daily activities | Prevent daily activities | Emergency department visit*  OR  Hospitalization |
| Myalgia | Does not interfere  with daily activities | Mild interference with daily activities | Prevent daily activities | Emergency department visit*  OR  Hospitalization |
| Arthralgia | Does not interfere  with daily activities | Mild interference with daily activities | Prevent daily activities | Emergency department visit*  OR  Hospitalization |

* It requires 12 hours or more of admission to a ward or emergency department for the management of the adverse event.

^†^ The value recorded should be measured at the largest diameter and as a continuous variable.

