### 9.3.5 Solicited Local and Systemic Reactions

Specific local and systemic reactions will be solicited (specifically asked of participants) while participants are in the study. These specific reactions, which are signs and symptoms, will be graded by a study clinician using the Toxicity Table for Grading Adverse Events (see Toxicity Tables 4, 5, 6). Grading will use predefined scales based on functional assessment or magnitude of reaction, where available. Where grading scales are not provided, the reaction will be graded for severity based on interference with participant functionally, as for all other AEs (see Section 9.3.2). Severity of redness, swelling and induration at the injection site should always be graded based on size.

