**For the first 100 subjects:**

- - Five or more participants who received at least one study injection to date experience severe (Grade 3/4) study injection-related local reaction of the same category other than measured erythema or induration.
  - Three or more participants who received at least one study injection to date experience a severe (Grade 3/4) study injection-related systemic reaction of the same category (excluding laboratory AEs, which will be monitored separately).
  - Three or more participants who received at least one study injection to date experience a severe (Grade 3) study injection-related abnormality in the same laboratory parameter.
  - Two or more participants who received at least one study injection to date experience a severe (Grade 4) study injection-related abnormality in the same laboratory parameter.

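### Table 4 ties chills Grades 2 and 3 to narcotic use and leaves Grade 4 blank, so disabling chills without a narcotic have no clear grade and are likely to be under-counted as severe

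*Protocol*

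**What the plan says.** Protocol Section 9.3.2 states that the severity of solicited, laboratory and unsolicited events "will be classified by a numeric scale ranging from 1 to 4". In Table 4 the chills row reads:

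- Grade 1: "Slight cold sensation; chills, teeth chatter"
- Grade 2: "Moderate chills in the entire body, it requires the use of narcotics"
- Grade 3: "Serious or prolonged, no response to narcotics"
- Grade 4: dashes only

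In the same table, "Any use of a narcotic analgesic" is enough for Grade 3 for injection-site pain and for headache. Fatigue/malaise, myalgia and arthralgia are graded by interference with activities: "Prevent daily activities" is Grade 3, and an emergency stay or hospitalisation is Grade 4.

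Section 9.3.5 adds a fallback: "Where grading scales are not provided, the reaction will be graded for severity based on interference with participant functionally". Sections 9.3.1 and 9.3.6 reclassify a solicited symptom that starts after day 7 as an unsolicited event, and Table 6 grades unsolicited events by interference with activities.

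Severity of reactions over the 7 days after each injection is part of the primary safety endpoint (Section 3.1). The systemic halting limb in Section 9.6 counts participants who "experience a severe (Grade 3/4) study injection-related systemic reaction of the same category". Three or more trigger it among the first 100 subjects, and 4% or more after that.

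**The concern.** Chills is one of seven solicited systemic reactions, and its grade depends on a treatment decision instead of on how badly the participant is affected. A participant with whole-body chills who cannot carry on normal activities, and who receives a non-narcotic medicine or nothing, does not clearly meet Grade 2 or Grade 3. Clinicians at three or more sites could grade that participant differently, and the likely direction of error is downward.

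Two uses of the data are exposed. One is the severity breakdown in the primary safety endpoint, which feeds the choice of one adjuvanted candidate from each of Groups 1 and 2 (Section 2.2.1). The other is the Grade 3/4 count in the systemic halting limb. Section 9.3.5 has a study clinician grade these reactions, so a defect in the scale enters the data at source.

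**Working it through.** The protocol gives no rate of chills, of severe chills or of narcotic use, so it has no figure of its own to reproduce. The defect itself is shown by comparing the text.

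**Step 1: the chills row against the rest of the plan**

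| Place | Rule | Chills row |
| --- | --- | --- |
| Section 9.3.2 | Four grades | Three; the only clinical row in Table 4 with an empty Grade 4 |
| Table 4, pain and headache | Any narcotic use is Grade 3 | Needing a narcotic is Grade 2 |
| Table 4, fatigue/malaise, myalgia, arthralgia | Activities prevented is Grade 3 | No activity criterion at any grade |
| Table 6, onset after day 7 | Activities prevented is Grade 3; emergency stay or hospitalisation is Grade 4 | Not applied inside the 7-day window |
| Section 9.3.5 fallback | Functional grading where no scale exists | A scale exists, so the fallback is not reached |

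Fever is the only other systemic row without an activity criterion, but it has temperature bands for all four grades.

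**Step 2: one case followed through.** Take chills that prevent daily activities, with no narcotic given. With onset on day 8, Table 6 gives Grade 3. With onset on day 3, Table 4 gives no clear Grade 2 or 3. The scale is weakest inside the window that the primary endpoint and the reactogenicity halting limbs use.

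**Step 3: what under-grading could do to the halting limb (illustration on assumed values).** Let p be the true proportion of all participants with related disabling chills, and s the share of those graded 3. The limb for the first 100 subjects is met by chills with probability

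P(X ≥ 3), where X ~ Binomial(100, p × s).

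At p = 5% and s = 1: 1 − (0.95^100 + 100 × 0.05 × 0.95^99 + 4950 × 0.05² × 0.95^98) = 1 − (0.006 + 0.031 + 0.081) = 0.88.

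| Assumed p | s = 1 | s = 0.5 | s = 0.25 | s = 0.1 | s = 0 |
| --- | --- | --- | --- | --- | --- |
| 1% | 8% | 1% | 0.2% | <0.1% | 0 |
| 2% | 32% | 8% | 1% | 0.1% | 0 |
| 3% | 58% | 19% | 4% | 0.4% | 0 |
| 5% | 88% | 46% | 13% | 1% | 0 |
| 8% | 99% | 77% | 32% | 5% | 0 |

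For the later 4% limb, evaluated once at N = 432, 0.04 × 432 = 17.28, so 18 participants are needed. At p = 5% the probability is 82% for s = 1, 3% for s = 0.5 and about 0 for s = 0.25.

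**The case against.** A reader might infer more than the text supports.

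**That disabling chills become Grade 1.** The Grade 1 cell opens with a slight sensation of cold. Its unqualified mention of chills could take in a worse event, but the fit is poor. The Grade 3 cell can also be read as two descriptors separated by a comma, so that serious or prolonged chills qualify alone. The nausea/vomiting row has a similar comma at Grade 3. The documents support an unclear grade, not a certain Grade 1.

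**That chills cannot count towards a halt.** Grade 3 exists for chills, and Section 9.6 pools Grades 3 and 4 in this limb, so an empty Grade 4 removes nothing from the count by itself. Inpatient hospitalisation makes the event serious (Section 9.3.7), and a single related serious event halts the study (Section 9.6). For such participants only the grade label is affected. The trial can also be suspended for any safety concern (Section 7.6.2), and the DSMB reviews the first 100 participants (Section 11.6).

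**That an adjuvant or dose effect on chills is hidden.** Percentages with each reaction are reported by group with exact intervals (Sections 11.2 and 11.5), so a difference in incidence stays visible. Only the severity split of one systemic term is blurred.

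**That an arm would show 0/54 instead of 3/54.** Three is about 5% of 54 (2.7), but the zero comes from stipulating that nobody receives a narcotic. Nor does a 5% rate in one arm carry over to the halting limb. Among the first 100 there are about 100/8 = 12.5 participants per arm, or 0.6 expected cases. With 12 participants the chance of three or more is 1 − 0.540 − 0.341 − 0.099 = 0.02, even with perfect grading. The probabilities in the working need the assumed rate across all participants.

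All of these limits stand. None of them supplies a clear Grade 2 or 3 for disabling chills in a participant who is not admitted and not given a narcotic.

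**Conclusion.** The point holds as an internal inconsistency with a probable direction of error. The chills row conflicts with Section 9.3.2, with its neighbours in Table 4 and with Table 6, and Section 9.3.5 does not resolve the conflict. Disabling chills without narcotic use have no clear Grade 2 or 3, may be graded differently across sites, and are likely to be under-counted as severe in one of seven systemic categories.

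Confidence is high on the inconsistency and lower on its effect, which depends on how clinicians read the row and on rates that the protocol does not give. The fall from 88% to 46%, 13% or 0 assumes a 5% rate of related disabling chills in all arms combined, independent participants and a single evaluation at 100. At a 1% rate the limb would seldom be met by chills under any grading (8% at most). The matter should be corrected because it touches a primary safety endpoint and a halting input, but it does not disable safety oversight.

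**What to change.** Before enrolment, reconcile the chills row with Section 9.3.2, Table 6, Section 9.3.5 and the neighbouring Table 4 rows. Every chills event should have one unambiguous grade, both inside and outside the 7-day window. In doing so, state whether the narcotic wording at Grades 2 and 3 is a necessary condition or a descriptor, and resolve the empty Grade 4 against the four-grade scale. The criteria themselves are for the sponsor to decide. Carry the reconciled wording into the diary and eCRF text so that sites grade alike.

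The cost is one table row and the matching data-collection text, with no change to the halting thresholds. More chills may be reported as severe, which makes the reactogenicity profile look less favourable and the systemic halting limb somewhat easier to reach.
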